### Eligibility

This study is open to both men and woman whom meet the following eligibility criteria: inpatient on the Harborne ward of the Queen Elizabeth hospital Birmingham, [name], UK; ≥65 years of age; frail according to the Fried Frailty Phenotype criteria^2^; ability to speak and read in English; not currently taking part in any other clinical trial which could potentially impact on or influence the findings of this study; not currently terminally ill with life expectancy less than the duration of the study; no severe sensory impairment which would profoundly impact on ability to undergo the intervention, even once appropriate adaptations have been made; anticipated by their care team to remain on the ward for ~21 days post-enrolment into the study.

### Interventions

All participants will undergo 10 sessions in total throughout the 2-week intervention in either one of the two interventions. All session will be conducted individually under the guidance of a qualified trainer. A maximum of one session will be performed each day, and sessions will not be performed on any more than a maximum of three consecutive days throughout the duration of the study (table 2).

**Table 2 T2:** Study timeline of all major events during each round of recruitment (SPIRIT schedule)

Week	Seated physical activity in ageing (SPAA) study timeline						
	Monday	Tuesday	Wednesday	Thursday	Friday	Saturday	Sunday
0	Identification + participant information sheet distribution	24 hours consideration period	Recruitment, eligibility screening and baseline assessments	Recruitment, eligibility screening and baseline assessments	Recruitment, eligibility screening and baseline assessments	Recruitment, eligibility screening and baseline assessments	–
1	Training	Rest	Training	Training	Rest	Training	Training
2	Training	Rest	Training	Training	Training	Rest	Training
3	Post-intervention assessment	Post-intervention assessment	Post-intervention assessment	Post-intervention assessment	Post-intervention assessment	Post-intervention assessment	–

SPIRIT, Standard Protocol Items: Recommendations for Interventional Trials.

#### Exercise intervention 1: specially adapted resistance training intervention

This intervention will be comprised of an intensive (5 days/week), short duration (2 weeks), ~35 min per session, machine-based resistance training intervention. The exercises performed will specifically target the lower limbs through a combination of multijoint strength and power training utilising a leg press and leg extension machine (figure 3).

**Figure 3 F3:**
[figure not shown]
Minato resistance training equipment utilised within the specially adapted resistance training intervention.

The maximal strength reference value (% one repetition maximum (1RM)), duration (35 min), type of exercise (multi-joint), loadings (60% 1RM (power), 80% 1RM (strength)) and volume (3 sets, 5–8 repetitions) are largely consistent with the position statement from the National Strength and Conditioning Association regarding resistance training in older adults.^30^

An outline of the protocol for each session can be found in figure 4.

**Figure 4 F4:**
[figure not shown]
Exercise intervention 1—specially adapted resistance training intervention protocol. 1RM, one repetition maximum.

#### Exercise intervention 2: MIOLI

This multi-component intervention will comprise of an intensive (5 days/week), short duration (2 weeks), ~35 min per session, chair-based exercise intervention. The exercises conducted will relate to strength, power, flexibility and aerobic capacity, consistent with the established MIOLI flexibility, aerobic capacity, balance and strength training programme for community-dwelling older adults. The exercises performed will predominantly targeting the lower limbs, but also incorporate the upper body and core.

An outline of the protocol for each session can be found in figure 5.

**Figure 5 F5:**
[figure not shown]
Exercise intervention 2—Move It Or Lose It (MIOLI) chair-based exercise intervention protocol.

### Dependent variables

#### Primary dependent variables

The primary dependent variables will relate to the eight primary areas of focus of feasibility studies^22^ (utilised to establish the feasibility of a proposed future clinical trial within this setting), relating to: acceptability, demand, implementation, practicality, adaptation, integration, expansion and limited-efficacy testing.

These dependent variables will be assessed through semi-structured interviews with study participants and focus groups with ward staff post-intervention. Participant uptake and adherence records will also be employed throughout. These methods seek to attain answers to the following questions and parameters relating to the eight primary areas of enquiry for this feasibility study outlined in further detail in table 1.

In order to enhance trustworthiness in the qualitative component of this research, several methods will be employed:

The researcher gathering the data will keep a reflective journal in which they will record information about themselves, their activities and the methods used. Field notes will include time, date and location, participant’s actual notes, and the researcher’s own questions and comments. This will lend to logging and documenting what is learnt about the study, the intervention, the setting, the participants, and used to refine focus for future interviews through assessing the following questions: What is important? What is it I need to find out more about? What would I want to focus on more closely if I could do the interview again, or in future interviews?^31^

Data will be gathered from study participants and ward staff in order to collect data from multiple sources (triangulate information). This study will also employ more than one researcher to analyse the qualitative data in order to enhance triangulation and validity.

Enough details will be given about the participants and the setting to make decisions about the quality of the findings from the qualitative analysis. Detailed descriptions about the participants experiences and the setting will be provided by the researcher.

In the qualitative data analysis, clarification of all possible researcher biases will be made known. For example, it will be articulated that the researcher is an advocate of physical activity as a means to promote health, prescribing to the theoretical and practical concept of exercise as medicine, and hence there may be some form of unconscious subjective bias in this context. However, it should also be noted that the researcher within this study is also an advocate of science to an equal or even greater extent, and as such any such bias in subjective analysis would potentially be counteracted in this sense.

Interviews—‘a conversation with a purpose’^32^ will be the primary method of data gathering utilised, as it enables large amounts of information to be gathered relatively quickly. Specifically, this study will employ semi-structured interviews, with open questions in a conversational format. There will be several predetermined themes, topics and questions to be discussed, specifically relating to the eight areas of focus of the primary dependent variables of this study. All interviews and focus groups will be audio recorded in order to facilitate future transcription. The qualitative element of this study will also explore opportunities for Patient and Public Involvement (PPI) in the research design of the proposed future clinical trial.

As this study will use a mixed-methods research approach, employing both qualitative and quantitative research methodologies, this will facilitate the potential for elaboration and expansion of these findings of individual methodologies through complementary analysis. The qualitative aspect of this feasibility study, aimed at assessing the primary dependent variables, will predominantly take a phenomenological approach to understand the experiences of individuals involved in the study.^33^

#### Secondary dependent variables

The secondary dependent variables relating to multidimensional health (comprising the proposed primary dependent variables of the future clinical trial) will be:

Physiological*: serum cortisol, dehydroepiandrosterone-sulphate (DHEAS), cortisol: DHEAS ratio, C reactive protein (CRP), IL-6, tumour necrosis factor alpha (TNFα), interferon gamma (IFNγ).

Functional: hand grip strength (Southampton protocol,^34^ Leg strength and power output,^35 36^ Short Physical Performance Battery (SPPB),^37^ Katz Index of Independence in Activities of Daily Living (Katz ADL),^38^ and the Fried Frailty Phenotype)^2^

Psychological/emotional: Geriatric Depression Scale,^39^ Hospital Anxiety Depression Scale.^40^

Cognitive: Standardised Mini-Mental State Examination.^41^

Social: Interpersonal Support Evaluation List (ISEL-12).^42^

*All blood samples will be obtained through venepuncture. Serum will be analysed for the physiological dependent variables relating to cortisol, DHEAS and CRP (assessed by commercial ELISA kit). Inflammatory cytokines (IL-6, TNFα, IFNγ) will be assayed using a multiplex commercial kit (R&D Systems). These specific physiological variables will be examined due to their association with the ageing process, and previous research which have both proposed and indicated that exercise is potentially capable of altering these variables.^43–48^

### Data collection

Data will predominantly be collected at two main time points: baseline and post-intervention (table 2).

#### Baseline assessment

Participants’ baseline sociodemographic and information for the secondary dependent variables will be collected between 5 and 2 days prior to intervention commencement. 1RM for the specially adapted resistance training equipment will also be assessed during this time period (after all baseline testing has been completed, and at least 24 hours after baseline testing which requires physical exertion, which may impact on the accuracy of the 1RM measurements). 1RM will be determined based on estimation from participants five repetition maximum (5RM) utilising the Epley formula: 1RM=w (1+r/30), where 1=weight, and r=repetitions.^36^ The protocol employed during obtainment of participants 5RM has been adapted from^35^ (online supplementary file 1). A balance screening will also be conducted prior to the commencement of the MIOLI intervention to determine whether participants should perform exercises standing, standing with chair support, or seated. In addition, the resistance bands which participants in the MIOLI intervention will use will similarly be assessed during this period; with three options corresponding to light, moderate and high resistances, prescribed to participants based on their initial ability and preference during their performance of the exercises in which the resistance bands will be utilised.

10.1136/bmjopen-2019-031159.supp1Supplementary data

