**Figure 2 F2:**
[figure not shown]
The independent variables of the proposed future clinical trial.

In order to ensure this present study is as scientifically valid as possible a number of precautions have been taken to protect the internal and external validity of the study within its methodological design: first, for each participant, all testing procedures (baseline and post-intervention (2 weeks)) will be conducted at approximately the same time of day (±2 hours). This will be controlled in order to protect the findings of the study from changes in the dependent variables which may be attributable to circadian variation rather than manipulation of the independent variables.^29^ The hypothesis of the study will not be divulged to participants prior to or during the conduction of the study in order to control for any potential degree of demand characteristics; a scenario where participants alter their behaviour and/or answers, in order to align with what they believe is potentially the ‘desired’ outcome of the study. All dependent variable testing sessions will take place at least 24 hours after the cessation of the previous training session for each participant. This will be implemented to ensure acute fatigue does not become a contributing factor to the results of the study, specifically relating to the secondary dependent variables, but also the feasibility of such practice during a proposed future clinical trial. The order in which dependent variables are tested will be counter-balanced throughout the study at each assessment timepoint in order to attempt to protect the study from practice effects, especially order effects, where a participant has been exposed to a specific order of testing before and as such performs better on subsequent testing procedures of the same material. Additionally, only one intervention will be run at a given time, protecting against potential subconscious selection bias among the research team relating to group allocation of participants. Finally, in order to increase the external validity of the study, eligibility criteria will be kept as minimalistic as possible (within the limits of safety and reason), in order to allow as inclusive a proportion of this population as possible, and in such producing findings which are applicable to not only those within the study, but to the greater population of frail geriatric hospital inpatients and particularly those within delayed transfer of care settings.

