#### Post-intervention assessment

Primary and secondary dependent variables will be assessed between 1 and 5 days post-intervention cessation. All assessments will be conducted at least 24 hours post the cessation of the last training session.

Adherence rates in the intervention will be recorded as the number of repetitions completed in a set (100% required for adherence to that exercise), and the number of exercises for which there was 100% adherence. If participants meet these parameters for each exercise session, they will be considered to be in 100% adherence to the intervention. For example, if a participant adheres to 100% of the intervention for nine sessions, but only 90% for one session, then they will have a 99% adherence rate. Adherence rates, whether high, or low, may signify that the interventions may have been too demanding, too easy or optimal. Information will also be collected throughout the study related to uptake and retention rates.

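### The baseline 5RM/1RM leg test has order and rest rules that are not carried to the post-intervention visit and clash with counter-balancing, so the within-arm leg-strength change may be biased

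*Protocol article*

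**What the plan says.** The Secondary dependent variables section of the protocol article lists "Leg strength and power output" among the functional outcomes, citing references 35 and 36. It has no restriction by arm.

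The Baseline assessment section says that "1RM for the specially adapted resistance training equipment will also be assessed during this time period". It places the test "after all baseline testing has been completed". A rest interval is set as well: the test comes "at least 24 hours after baseline testing which requires physical exertion, which may impact on the accuracy of the 1RM measurements". The section adds that "1RM will be determined based on estimation from participants five repetition maximum (5RM) utilising the Epley formula". The 5RM procedure is referenced to 35 and the Epley formula to 36, with detail in a supplementary file that is not shown. The section then gives set-up steps for MIOLI: a balance screen and the choice of resistance bands.

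The Post-intervention assessment section gives one rest condition: "All assessments will be conducted at least 24 hours post the cessation of the last training session". The Design overview has the same rule in general form: "All dependent variable testing sessions will take place at least 24 hours after the cessation of the previous training session for each participant". It also says that the order of the dependent-variable tests is counter-balanced at each assessment timepoint.

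**The concern.** The protocol itself names the threat, that earlier exertion may make the 1RM less accurate, and guards against it at one visit only. The reason applies equally at the other visit. A change score needs the same measurement conditions at both ends. If the first measurement is always rested and the second sometimes follows other physical tests, part of the measured change reflects the testing order.

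There is also a direct conflict at baseline. A test that always comes last cannot be in a counter-balanced order, so staff cannot follow both the Design overview and the Baseline assessment section.

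Finally, the baseline test is described by reference to the resistance equipment, and MIOLI is then given other set-up steps. Only one intervention runs at a time, so staff in a MIOLI round have no explicit instruction to do the 5RM.

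What is at stake is the leg-strength change. The resistance intervention targets the lower limbs, the variable is a proposed primary variable of the future trial, and the Statistical methods section says these analyses are to inform that trial's design.

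**Working it through.** **1. Is the 1RM test the leg-strength outcome?** The outcome list cites references 35 and 36. The baseline section cites 35 for the 5RM procedure and 36 for the Epley formula. The article describes no other leg-strength test. The identity is a strong inference, not a statement in the text.

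**2. Rules side by side.**

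| | Baseline | Post-intervention |
|---|---|---|
| Rest since training | no training yet | at least 24 h |
| Rest since other exertional tests | at least 24 h | none written |
| Position of the 1RM test | after all other tests | none written |
| General order rule | counter-balanced | counter-balanced |

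The protocol does not list which tests count as exertional. The likely ones are the SPPB, hand grip, and the grip and walking components of the Fried phenotype. Under counter-balancing, some participants would reach the leg test after these.

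**3. Can equal conditions fit the calendar?** In Table 2, training starts on the Monday of week 1 and ends on the Sunday of week 2.
- Baseline: Wednesday to Saturday of week 0 are 5, 4, 3 and 2 days before the start, which matches the stated window. To leave 24 h, exertional tests must be finished by Friday.
- Post-intervention: Monday to Friday of week 3 are 1 to 5 days after the last session, which matches the stated window. Two separate test days fit. (Saturday, also shown in Table 2, is day 6 and lies outside the stated 1 to 5 days.)

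**4. Possible size.** The plan has no figure to reproduce and gives no fatigue effect, so all values here are assumptions. Let g be the true gain, f the proportional loss in 5RM when tested after other exertion, and s the share of participants so tested post-intervention:

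observed gain = (1 + g)(1 − f·s) − 1

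Epley at five repetitions is a constant factor, 1 + 5/30 = 1.167, so a proportional loss in 5RM passes unchanged to 1RM. With g = 10%:

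| Loss f | Half affected (s = 0.5) | All affected (s = 1) |
|---|---|---|
| 2% | 1.10 × 0.990 − 1 = 8.9% | 1.10 × 0.98 − 1 = 7.8% |
| 5% | 1.10 × 0.975 − 1 = 7.25% | 1.10 × 0.95 − 1 = 4.5% |
| 10% | 1.10 × 0.950 − 1 = 4.5% | 1.10 × 0.90 − 1 = −1.0% |

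**5. Contrast between arms.** Take assumed true gains of 15% and 5%, a difference of 10 points, with the same loss in all participants of both arms. The observed difference is (1.15 − 1.05)(1 − f) = 9.8, 9.5 or 9.0 points for f = 2%, 5% or 10%. The within-arm change is exposed; the contrast is barely touched.

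**6. MIOLI baseline.** The 1RM sentence names equipment, not an arm. The same section collects the secondary variables at baseline for participants generally, and the Statistical methods section analyses both interventions at baseline and post-intervention. The intention therefore points to testing both arms, but the 1RM sentence does not say so.

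**The case against.** The strongest counter-argument is that the 1RM is only a load-setting step. The text says it is also assessed, once baseline testing is complete, and the MIOLI set-up steps follow directly. The resistance loads are set as percentages of 1RM. On that reading, leg strength belongs to the ordinary battery, under the same rules at both visits, and the asymmetry disappears. This is possible, but it leaves the outcome with no described test and does not explain the shared references. The text needs to settle it either way.

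It can also be said that this is a condensed article, that the 5RM procedure is in an unseen supplement, and that test sequencing is normally left to fuller documents. That would answer a simple omission. It does not answer two order rules in the same article that cannot both be followed at baseline, or a stated safeguard applied to one visit only.

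Three stronger readings are tempting, and the document does not support them.
- *The change scores are biased and most of the gain is lost.* No fatigue effect is given, the post-intervention window allows rested testing, and large losses need both a large assumed effect and every participant tested fatigued. The Design overview also recognises practice effects, which could raise later scores, so the net direction of error is not established.
- *Post-intervention testing has no protection from fatigue.* The 24 h rule after training covers all assessments. Only separation from other exertional tests is unwritten.
- *Leg-strength change will be missing for all 15 MIOLI participants.* The outcome list, the general baseline sentence and the planned analysis all cover both arms.

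**Conclusion.** The point stands as an inconsistency that should be corrected. The Design overview, Baseline assessment and Post-intervention assessment sections give order and rest rules that conflict at baseline and differ between visits. The within-arm leg-strength change may therefore be biased, and the fatigue component would act towards a smaller gain. This rests on the strong but unstated inference that the 1RM test is the leg-strength outcome, and on some participants being tested after other exertion post-intervention. The size cannot be derived from the document; the figures above show only how it depends on the assumptions. Whether MIOLI participants have the baseline test should be made explicit, although the rest of the text suggests that they do.

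The consequence is limited. This is one of many secondary variables in a study of about 30 participants with no power calculation. The protocol already asks for caution in reading these results, and the primary feasibility assessment is largely unaffected.

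**What to change.** Reconcile the three sections with a short statement that:
- the 5RM/Epley 1RM test is the leg-strength outcome;
- it is done in both arms, MIOLI included, at baseline and post-intervention;
- it is exempt from counter-balancing, which continues to apply to the other tests;
- the same position in the battery and the same minimum interval from other exertional tests apply at both visits.

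If the 1RM is instead only a load-setting test, say so and name the test that measures leg strength.

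The cost is protocol wording, plus a post-intervention battery split over two days for some participants. That is a real burden for frail inpatients, but it fits the existing window of 1 to 5 days and mirrors what the baseline rule already requires.

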#### Post-intervention assessment

Primary and secondary dependent variables will be assessed between 1 and 5 days post-intervention cessation. All assessments will be conducted at least 24 hours post the cessation of the last training session.

Adherence rates in the intervention will be recorded as the number of repetitions completed in a set (100% required for adherence to that exercise), and the number of exercises for which there was 100% adherence. If participants meet these parameters for each exercise session, they will be considered to be in 100% adherence to the intervention. For example, if a participant adheres to 100% of the intervention for nine sessions, but only 90% for one session, then they will have a 99% adherence rate. Adherence rates, whether high, or low, may signify that the interventions may have been too demanding, too easy or optimal. Information will also be collected throughout the study related to uptake and retention rates.

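### The all-or-nothing adherence score depends on how many exercises a session holds, merges absence with near-completion, and is tied to no conclusion

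*Protocol article*

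**What the plan says.** The rule is in the Protocol article, Post-intervention assessment. Adherence is recorded as the "number of repetitions completed in a set (100% required for adherence to that exercise") together with a count of the exercises that meet that standard. The worked example runs: "if a participant adheres to 100% of the intervention for nine sessions, but only 90% for one session, then they will have a 99% adherence". The same paragraph ends its account of adherence with: "Adherence rates, whether high, or low, may signify that the interventions may have been too demanding, too easy or optimal".

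Three other places bear on the scoring:

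- Interventions: "All participants will undergo 10 sessions in total throughout the 2-week intervention in either one of the two interventions".
- Exercise intervention 1: the resistance sessions combine strength and power work "utilising a leg press and leg extension machine". The text below Figure 3 gives the "volume (3 sets, 5–8 repetitions") and separate loads for power and for strength.
- Exercise intervention 2: the Move It Or Lose It (MIOLI) sessions cover strength, power, flexibility and aerobic work for the lower limbs, upper body and core. The text gives no exercise count; the session outlines are in Figures 4 and 5, which are not shown.

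Table 1 lists adherence as a method of assessment for Demand and for Limited-efficacy testing. Both are among the eight areas that make up the primary dependent variables.

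**The concern.** Adherence should tell the team whether frail inpatients can and will do the programme. Three features of the stated rule work against that.

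First, the penalty for a missed repetition is set by how many exercises the session contains, not by how much exercise was missed. The same behaviour can therefore yield different rates in two programmes with different numbers of exercises.

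Second, one percentage has to carry both coming to the session and finishing everything in it. These point to different design changes for the future trial.

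Third, the interpretive sentence allows a high rate and a low rate the same three meanings, so the article links no adherence level to any conclusion.

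At stake is a programme that was delivered almost in full but reports a middling adherence rate, with nothing in the plan to say how that rate should be read.

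**Working it through.** **Inputs.** Ten sessions per participant (Interventions). All-or-nothing scoring per exercise, and the example (Post-intervention assessment). Two machines, 3 sets, 5–8 repetitions (Exercise intervention 1). The number of scored exercises per session, k, is not in the text. For the resistance arm I take k = 2 (one per machine) or k = 4 (strength and power scored separately on each machine). For MIOLI I assume 6 to 20.

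**The plan's own figure.** Nine sessions at 100% and one at 90%: (9 × 100 + 90)/10 = 99.0%. This reproduces the stated 99%, so the overall rate is the unweighted mean of ten session scores.

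**Cost of one missed repetition.** If a session score is 100 × (exercises fully completed)/k, one missed repetition gives a session score of 100 × (k − 1)/k. If it happens in one session only, the overall rate is (900 + session score)/10.

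| Arm | k | Session score | Overall, one such session |
|---|---|---|---|
| Resistance | 2 | 50% | 95.0% |
| Resistance | 4 | 75% | 97.5% |
| MIOLI (assumed) | 6 | 83.3% | 98.33% |
| MIOLI (assumed) | 10 | 90% | 99.0% |
| MIOLI (assumed) | 20 | 95% | 99.5% |

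The penalty ratio, resistance to MIOLI, is the inverse ratio of the counts: 6/4 = 1.5 at the narrow end, 10/2 = 5 in the middle, 20/2 = 10 at the wide end.

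**Share of repetitions actually missed, resistance arm.**

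- k = 2: 2 × 3 × 5 = 30 to 2 × 3 × 8 = 48 repetitions. One missed is 1/30 = 3.3% to 1/48 = 2.1%, so 96.7–97.9% was done, against a session score of 50%.
- k = 4: 60 to 96 repetitions. One missed is 1/60 = 1.7% to 1/96 = 1.0%, so 98.3–99.0% was done, against a session score of 75%.

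Scored by repetitions, one such session in ten would give 99.67–99.79% overall (k = 2) or 99.83–99.90% (k = 4), in place of 95.0% or 97.5%. If one repetition were missed in every session, the all-or-nothing rate would be 50% or 75% overall, with 96.7–99.0% of repetitions done.

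**Merging with attendance.** If a missed session scores zero, a participant who attends 5 of 10 and completes them fully has 5 × 100/10 = 50%. With k = 2, that equals the rate of someone who attends all ten and drops one repetition each time.

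**Can the example occur in the resistance arm?** With k = 2 the possible session scores are 0, 50 and 100; with k = 4 they are 0, 25, 50, 75 and 100. Neither contains the 90% in "but only 90% for one session, then they will have a 99% adherence rate"; among whole exercise counts it needs k = 10 or a multiple of 10. Counting sets does not help: with 6 sets the nearest scores are 5/6 = 83.3% and 100%, with 12 sets 10/12 = 83.3% and 11/12 = 91.7%. As a share of repetitions 90% can occur (27 of 30, for instance). But then partly completed exercises earn credit, which the 100% requirement excludes.

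**The case against.** The strongest reply is that much of the arithmetic depends on figures that cannot be seen. The text names two machines, not two scored exercises, and gives no count for MIOLI. That is right, and it limits the claim. A reader might infer that one missed repetition always costs half a session in one arm and far less in the other. The documents support only a half or a quarter in the resistance arm, and a probably smaller cost in MIOLI whose size cannot be fixed.

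A second reply is that the article never says outright that a session percentage is the share of completed exercises, and that the example is generic to both programmes. This also stands, and the result is conditional on that reading. But the alternative, a share of repetitions, conflicts with the stated 100% requirement, so the definition needs settling either way.

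Third, a reader might infer from the 5–8 range that the repetition target is undefined. The documents do not support this: Figure 4 gives the session protocol and may fix a target within the range.

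Fourth, no between-arm test of adherence is described, and feasibility is judged mainly from interviews and focus groups, with uptake and retention added. So it would be wrong to say that no result could count against feasibility. What stands is narrower: no level of adherence is tied to a conclusion. The disputed sentence can be read as a caution against interpreting a rate alone, but it does not say so.

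Finally, repetitions per set are recorded, so a graded score can still be derived. That lowers the severity and makes the correction easy.

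**Conclusion.** The point holds as a modest, cheaply corrected weakness in a stated scoring rule. On the natural reading, one missed repetition takes 50 or 25 points off a resistance session in which about 1–3% of repetitions were missed. In a single session of ten the effect on the overall rate is small (95.0% or 97.5%). It becomes large only if near-misses recur (50% or 75% if in every session).

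The rates of the two arms are not on one scale if their exercise counts differ, which is likely from the descriptions but not shown. The conflict between the 90% example and the rule in the resistance arm holds for k = 2 and k = 4. The equivalence with half attendance needs k = 2 and missed sessions scored as zero. The objection to the interpretive sentence depends on none of these assumptions.

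**What to change.** In Post-intervention assessment, replace the single rate with two, reported separately by arm over all 10 scheduled sessions for everyone who starts:

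- (a) sessions attended out of 10;
- (b) repetitions completed out of repetitions prescribed, as a continuous percentage. For items not counted in repetitions, as some flexibility or aerobic items may be, use the share of the prescribed item completed.

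Keep the all-or-nothing rate only as a supplementary figure, and reword the 90% example to match whichever definition it illustrates. Replace the interpretive sentence with a statement that low attendance or low completion counts against feasibility and is read alongside the interviews.

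The cost is a wording change and re-scoring of records already kept; the downside is two adherence figures in place of one. Progression limits and a score based on load could be added, but they are optional and the point does not rest on them.
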